**Figure 1 F1:**
[figure not shown]
The schedule of enrolment, interventions, and assessments. DLQI = dermatology life quality index, F = months, IL-23 = interleukin 23, IL-17 = interleukin 17, PASI = Psoriasis area and severity index, T = weeks, TNF-α = tumor necrosis factor α, VEGF = vascular endothelial growth factor; .

**Figure 2 F2:**
[figure not shown]
Flow diagram of study design.

###  Participants

2.2

#### Inclusion criteria

2.2.1

The inclusion criteria are: inpatients; patients corresponding to diagnosis standards psoriasis vulgaris with Western Medicine; patients corresponding to diagnosis standards psoriasis vulgaris with the blood-heat syndrome of Traditional Chinese Medicine; patients corresponding to the progressive stage of psoriasis vulgaris; patients diagnosed with psoriasis vulgaris between 18 and 65 years old, regardless of gender and course of the disease; patients that have provided informed consent, and voluntarily accept and cooperate with treatment, examination, and observation.

#### Exclusion criteria

2.2.2

The exclusion criteria are: pregnant or lactating women; patients allergic to drugs or drug components; comorbid psoriatic arthritis, pustular psoriasis, or erythrodermic psoriasis; patients who have taken steroids within the preceding 2 weeks and/or taken retinoids or topical steroids within the preceding week; patients with severe primary diseases, such as cardiovascular, cerebrovascular, liver, kidney, or hematopoietic system diseases; patients with active pulmonary tuberculosis, acute or chronic hepatitis, or other infectious diseases; psychotic patients, epileptic patients, or other patients without self-restraint; external injury or infection on the body surface; and female patients with menstruation during hospitalization.

#### Sample size calculation

2.2.3

According to the calculation formula of sample size in clinical trials,^[7]^ the necessary estimated loss rate is 10%, and the total sample size is 288 cases, with 36 cases per group. There will be 36 participants assigned to each group, including 36 cases in the basic treatment group, 36 cases in the control group, and 36 cases in each of the 6 observation groups.

#### Randomization and blinding

2.2.4

Randomized grouping will be done using IBM SPSS statistics (version 22.0) software's random number generator.

#### Allocation concealment

2.2.5

The random allocation form will be made in triplicate and kept in opaque envelopes. The project director, the pharmacy director, and the statistician will each keep one copy of the allocation form. At the end of the test, 3 random allocation forms will be simultaneously unsealed during a face-to-face meeting. If one or more of the seals are damaged, an explanation will be needed. Otherwise, the grouping information will be declared secret, or the test will be considered invalid.

#### Blind method

2.2.6

Because the 3 groups’ intervention measures are not the same, blinding methods are not applicable.

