## Abstract

**Background::**

Chinese herbal bath has long been used in the curative treatment of psoriasis vulgaris. However, there is no unified standard protocol for Chinese herbal bath. Many factors affect the curative effect of Chinese herbal bath, such as water temperature, bath concentration, and soaking time. Most studies involving Chinese herbal bath has described the bath generally, and few studies have investigated the factors that might contribute to the efficacy of Chinese herbal bath. Here we describe a protocol to evaluate the efficacy and safety of various bathwater temperatures and herbal concentrations on psoriasis vulgaris, and their effect on serum vascular endothelial growth factor (VEGF), tumor necrosis factor α (TNF-α), interleukin 23 (IL-23), and interleukin 17 (IL-17). These data could be useful for optimizing Chinese herbal bath treatments.

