**Methods::**

In this randomized controlled trial, we planned to recruit 288 hospitalized atients with psoriasis vulgaris aged 18 to 65 years. All participants who meet the inclusion criteria will be randomly assigned to the observation group, the control group, or the basic treatment group. The observation group will be divided into 6 sub-groups according to water temperatures and bath concentrations, designated as observation groups 1 to 6. Thirty-six participants will be assigned to each group. The basic treatment group will be given co-qingdai capsule, po 2 g tid; compound glycyrrhizin tablet, po 75 mg tid; AA Skincare jojoba Oil, us.ext qd. The observation group will be given a Chinese herbal bath at the same time as the basic treatment. The control group will be given ozone hydrotherapy at the same time as the basic treatment. The entire treatment course will last for 2 weeks. The following parameters will be compared in each group, before and 2 weeks after treatment: the psoriasis area and severity index score (PASI), pruritus score, clinical efficacy, and dermatology life quality index score (DLQI); serum levels of serum VEGF, TNF-α, IL-23, and IL-17; and confocal laser scanning microscope images.

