#### The bathing process

2.3.5

For bathing, the following equipment is needed: a wooden bathtub, a disposable tub bag, cotton towels, slippers, and a constant temperature heater (Little Magneto Xiaoyubao, Manufacturer: Foshan Xiaociren Electric Appliance Industry Co., Ltd, model CA01).

Before the Chinese herb bath, the nurse will set the temperature of the bathroom to 20 to 22 °C,^[12]^ put the disposable tub bag in the bathtub, pour in the corresponding proportion of Chinese Medicine liquid and water, then add the constant temperature heater, setting the temperature and time. The patient will sit in the bath bucket, soak the torso and limb in the bathwater, and gently wipe their skin with a towel. The nurse will regularly check the situation in the bathroom and ask whether the patient has any discomfort, such as dizziness, dyspnea, palpitation, chest tightness, or other symptoms. If the patient reports any of the above discomforts, the herb bath will be stopped, and the nurse will assist the patients in returning to the ward, closely observe the condition, and ask the doctor to give treatment. After the Chinese herb bath is over, to avoid getting cold, the patients should thoroughly dry themselves with a towel. During the 2-week treatment period, the patient will take one herbal bath per day, with each bath lasting 30 minutes.

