### Primary outcome

2.4

Psoriasis area and severity index^[13]^ scores will be evaluated as the primary outcome. The PASI is a reliable, reproducible, and responsive instrument. This index has good internal consistency, intra-observer reliability, and inter-observer reliability, and is considered as the gold standard for assessing the severity of cutaneous manifestations in psoriasis. Therefore, this index will be used as our primary outcome.^[14]^

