#### Dermatology life quality index

2.5.2

According to the DLQI questionnaire,^[16]^ patients need to complete ten questions about the impact of the disease on their quality of life (0 = none; 1 = slight; 2 = serious; 3 = very serious). The DLQI scores are calculated by summing the scores for each question. The maximum value is 30, and the minimum value is zero. The higher the scores, the greater the impact on the quality of life.

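### Section 2.2.6 rules out all blinding for a reason that does not reach the six herb-bath arms, where patients could at least be left unaware of their assigned temperature and concentration

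*Protocol article*

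**What the plan says.** The blinding policy in section 2.2.6 of the protocol article is one sentence. It refers to three groups and concludes that, because their "intervention measures are not the same, blinding methods are not applicable", nothing further is needed.

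The trial has eight arms, not three. The abstract's Methods paragraph states: "The observation group will be divided into 6 sub-groups according to water temperatures and bath concentrations, designated as observation groups 1 to 6". The abstract's Background gives the aim as to "evaluate the efficacy and safety of various bathwater temperatures and herbal concentrations on psoriasis vulgaris", which is a question about contrasts among those six arms.

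Section 2.3.4 gives a single herbal prescription for all six. Section 2.3.5 gives a single procedure, with one list of equipment and one schedule: "the patient will take one herbal bath per day, with each bath lasting 30 minutes". Before the bath, the nurse is to "pour in the corresponding proportion of Chinese Medicine liquid and water, then add the constant temperature heater, setting the temperature and time". The patient then sits in the tub to "soak the torso and limb in the bathwater".

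On outcomes, section 2.4 says "Psoriasis area and severity index^[13]^ scores will be evaluated as the primary outcome". Section 2.5.2 makes the DLQI a patient questionnaire: "patients need to complete ten questions about the impact of the disease on their quality of life". Section 2.5.1 lists the pruritus score as secondary without saying who rates it. In section 2.3.5 the nurse asks the patient about discomfort, and a positive answer ends the bath.

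Section 2.2.5 keeps three copies of the allocation form in opaque envelopes until the end of the trial and treats the grouping as secret.

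**The concern.** The stated reason does not support the stated conclusion. No patient can be kept unaware of whether the treatment is a herb bath, an ozone bath or no bath. That does not make it impossible to withhold the assigned level from a herb-bath patient, and the section does not consider those arms.

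What is at stake is the comparison of temperatures and concentrations on outcomes that depend on the patient's own report. A patient who knows that the assigned bath is the weaker or cooler one may answer the DLQI differently, or be quicker or slower to report discomfort. The same would apply to itch if it is self-rated. An expectation effect of this kind is mixed with the effect of the bath condition, and no later analysis can separate the two.

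**Working it through.** **1. How much of the trial the reason leaves uncovered.** Inputs: 36 per group and 288 in total (section 2.2.3), with six observation groups, one control group and one basic group.
- Total: 8 × 36 = 288, which agrees with the protocol.
- Herb-bath arms: 6 × 36 = 216 patients, and 216 / 288 = 75%.
- Pairwise contrasts among the six: 6 × 5 / 2 = 15. Among all eight: 8 × 7 / 2 = 28.

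The reason in 2.2.6 concerns differences between the three main groups. It covers none of the 15 contrasts within the herb-bath arms.

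**2. Whether non-disclosure fits the procedure.**
- Prescription (2.3.4): the same in all six arms.
- Equipment, frequency and duration (2.3.5): the same in all six arms.
- Temperature and concentration: different by design. The nurse sets both before the patient gets in.
- Design (2.1): parallel-group, so a patient is assigned one condition only and has no second assigned bath to compare.
- Allocation (2.2.5): sealed to the end.

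Nothing here requires the patient to be told the level. Temperature is felt, however, and concentration may show in colour or smell. The latter is an assumption, since the text does not describe the liquid's appearance.

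**3. Which outcomes are exposed.** The DLQI is patient-completed, so it is exposed. Bath discomfort is what the patient reports, so it is exposed. Pruritus is exposed only if patients rate it. PASI is a severity score, and section 2.7 has dermatologists collect the data, so it is not the outcome affected by this route.

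**4. Illustration of size.** The protocol gives no figure for expectation bias, so the bias b is assumed at 0.1, 0.2 and 0.3 SD, with no true difference. The test is the independent-sample t test of section 2.7 at 0.05, taken as two-sided (the protocol does not say). With n per arm:
- degrees of freedom = 2n − 2
- noncentrality = b × √(n/2)
- chance of P<.05 = probability that a noncentral t with these values exceeds the critical value in either direction

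The loss rate in section 2.2.3 is 10%, so 36 × 0.9 = 32.4, or about 32 evaluable per arm.

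| Assumed bias (SD) | Noncentrality, n = 36 | Chance of P<.05, 36 v 36 | Noncentrality, n = 32 | Chance of P<.05, 32 v 32 |
|---|---|---|---|---|
| 0 | 0 | 5.0% | 0 | 5.0% |
| 0.1 | 0.42 | 7.0% | 0.40 | 6.8% |
| 0.2 | 0.85 | 13.3% | 0.80 | 12.4% |
| 0.3 | 1.27 | 24.1% | 1.20 | 21.9% |

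A normal approximation at n = 32 gives 6.9%, 12.6% and 22.4%, so the result does not depend on the choice of method.

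**The case against.** The strongest case against the point has four parts.

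**Patients can perceive the condition.** The arms differ in exactly the two features under test, and patients sit in the water for 30 minutes a day for two weeks. This stands in large part. A reader might infer that the six arms use the same bath, that patients could be fully masked and that the exposure is therefore needless. The documents do not support that. The prescription and procedure are shared, but the bath is not. The temperature levels are not given in the text and the body of Table 1 is not shown, so how easily patients could tell conditions apart cannot be judged. What remains is that feeling warm water differs from being told one's level, and that temperature gives nothing away between arms that share it.

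**No passage says patients are told their level.** This also stands. The consent pages are not available, and section 2.2.5 points towards secrecy. The point is therefore that 2.2.6 gives up masking for these arms without a reason that covers them, not that disclosure is planned. The poor fit between 2.2.5 and 2.2.6 needs resolving in any case.

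**The exposed outcomes are secondary.** This stands. It would be wrong to infer from this point that the primary PASI comparison is biased. Masking of PASI assessors or of the analyst is a separate matter.

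**The size is assumed.** This stands too. A reader might be tempted to pool arms over one factor and obtain larger false-positive rates. That needs a crossed layout and a pooled factor analysis, and the text shown states neither, so only pairwise figures are given.

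**Conclusion.** The point holds in limited form. The reason in section 2.2.6 does not extend to observation groups 1 to 6, which hold 75% of the patients and carry the stated question. The plan thereby gives up a partial safeguard for the DLQI and for reported bath discomfort, and for pruritus if it is self-rated.

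On the assumed biases of 0.1 to 0.3 SD, the false-positive chance per pairwise comparison rises from 5% to between about 7% and 24% (7% to 22% after the planned loss). These figures show how sensitive the comparison is. They do not estimate a bias, for which the documents give no basis. The change is worth making because it is cheap and concerns the contrasts the trial was set up to study. It does not call the primary outcome into question.

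**What to change.** Amend section 2.2.6 along these lines:

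- Patients in observation groups 1 to 6 know that they receive a herb bath but are not told the assigned concentration or set temperature.
- The nurse prepares the bath before the patient enters, keeps the heater setting out of the patient's view, and does not disclose the level.
- Patients in the ozone and basic groups cannot be masked. Nor can the bath nurse, who mixes the liquid, sets the heater and asks about discomfort. Coding the supplied liquid would not change that.

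At week 2, ask each herb-bath patient which condition they think they had, and report the answers by arm. Reconcile 2.2.6 with 2.2.5, so that it is clear from whom the allocation is kept secret and until when. State in 2.5.1 who rates pruritus.

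The cost is revised wording in 2.2.6 and in the consent text, a way of hiding the heater setting, an instruction to the nurse, and one extra question. No arm, bath condition or clinical rule changes. The limitation should be stated openly: masking is partial and mainly useful for concentration among arms at the same temperature, since heat is felt, colour or smell may show, and patients on the same ward may compare.

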#### Participants recruitment

2.2.7

The participants will be recruited from the Hospital of Chengdu University of Traditional Chinese Medicine and Chengdu Yinkang Psoriasis Hospital by an open recruitment method. Participants will be screened according to the inclusion and exclusion criteria. The recruiting members will be [name], associate chief physician [name], associate chief physician [name], attending physician [name], and attending physician [name].

#### Collection of general information of participants

2.2.8

The data will be collected by [name] and [name]. The general information collected will include sex, age, height, weight, race, occupation, marital status, birthplace, home address, telephone number, disease season, past history, allergic history, and family history.

### Intervention

2.3

#### Basic treatment

2.3.1

All of the included cases will be given the basic treatment which has three components: a co-Qingdai capsule [recommended according to expert consensus on the treatment of psoriasis vulgaris with Chinese patent medicine (2014)^[8]^; manufactured by Tianning Pharmaceutical Co., Ltd., Shanxi Pharmaceutical Holding Group; National medicine permission number Z20010157; 0.5 g per granule; usage and dosage: po 2 g tid], glycyrrhizin tablets (recommended according to the guideline for the diagnosis and treatment of psoriasis in China, 2018 complete edition^[5]^; manufactured by Minophagen Pharmaceutical Co., Ltd; National medicine permission number J20130077; 25 mg per tablet; Usage and dosage: po 75 mg tid), AA Skincare jojoba oil (recommended according to the general topical therapies of psoriasis vulgaris^[9]^; manufactured by AA Skincare Ltd; National make-up with Chinese characters number J20128945; 100 ml per bottle; external use, once a day).

#### The basic group treatment

2.3.2

The basic treatment group will be given only basic treatment.

#### The control group treatment

2.3.3

The control group will be given ozone hydrotherapy at the same time as the basic treatment. The required tools are: a wooden bathtub, a disposable bathtub bag, cotton towels, slippers, and an ozone hydrotherapy instrument (Hunan Haizhi Medical Technology Co., Ltd., type HZ-261A).

The ozone water will be prepared as follows: the oxygen machine generates the oxygen that, via the ozone generator, generates a high ozone concentration (4 mg/L) in the bathwater. The participants will bath once per day, for 30 minutes.

#### The observation group treatment

2.3.4

The observation group will be given Chinese herbal bath at the same time as the basic treatment.

The Chinese herbal bath prescription will be composed of: phellodendron (30 g), rhubarb (15 g), sophora flavescens (30 g), purslane (30 g), fructus kochiae scopariae (30 g), glycyrrhiza (30 g), mirabilite (20 g), alumen (10 g), and borneol (3 g).

All of the above Chinese herbs are provided by the Chinese medicine pharmacy of Chengdu Yinkang Psoriasis Hospital and decocted by the boiling machine of Chengdu Yinkang Psoriasis Hospital. According to the methods of the decoctum preparation and the standardization of decoction preparation in “Treatise on Exogenous Febrile Diseases,”^[10]^ and the management standard of Chinese medicine decoction room,^[11]^ the decoction amount is 1 L per dose. Table 1 shows Chinese medicine liquid and diluent of different concentrations.

**Table 1 T1:**

The Chinese Medicine liquid and diluent for different concentrations.

#### The bathing process

2.3.5

For bathing, the following equipment is needed: a wooden bathtub, a disposable tub bag, cotton towels, slippers, and a constant temperature heater (Little Magneto Xiaoyubao, Manufacturer: Foshan Xiaociren Electric Appliance Industry Co., Ltd, model CA01).

Before the Chinese herb bath, the nurse will set the temperature of the bathroom to 20 to 22 °C,^[12]^ put the disposable tub bag in the bathtub, pour in the corresponding proportion of Chinese Medicine liquid and water, then add the constant temperature heater, setting the temperature and time. The patient will sit in the bath bucket, soak the torso and limb in the bathwater, and gently wipe their skin with a towel. The nurse will regularly check the situation in the bathroom and ask whether the patient has any discomfort, such as dizziness, dyspnea, palpitation, chest tightness, or other symptoms. If the patient reports any of the above discomforts, the herb bath will be stopped, and the nurse will assist the patients in returning to the ward, closely observe the condition, and ask the doctor to give treatment. After the Chinese herb bath is over, to avoid getting cold, the patients should thoroughly dry themselves with a towel. During the 2-week treatment period, the patient will take one herbal bath per day, with each bath lasting 30 minutes.

#### Matters of attention when participating in Chinese herb bath

2.3.6

Women are forbidden from taking Chinese herb bath during menstruation. The participants should not fast while participating in the Chinese herb bath trial and avoid using bath products outside of the test.

#### Trial course and follow-up

2.3.7

The treatment course will last 2 weeks, and the outcomes will be recorded before treatment and during the second week of treatment. After the 2 weeks of treatment, the patients will be followed up once per month for the next 6 months.

### Primary outcome

2.4

Psoriasis area and severity index^[13]^ scores will be evaluated as the primary outcome. The PASI is a reliable, reproducible, and responsive instrument. This index has good internal consistency, intra-observer reliability, and inter-observer reliability, and is considered as the gold standard for assessing the severity of cutaneous manifestations in psoriasis. Therefore, this index will be used as our primary outcome.^[14]^

### Secondary outcome

2.5

#### The effective rate of treatment, pruritus score, and incidence of adverse reactions

2.5.1

The Guiding Principles for Clinical Research of New Traditional Chinese Medicine (trial) is the general evaluation standard in China. According to the evaluation standard, the effective rate of treatment, pruritus score, and incidence of adverse reactions are taken as secondary outcomes.^[15]^

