### Safety evaluation

2.6

According to the safety assessment in randomized controlled clinical trials,^[17]^ the safety of this study will be evaluated by adverse events, routine blood tests, and liver and kidney function tests.

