### Data collection and management

2.7

All data will be analyzed according to the intention to treat principle. The missing value will be dealt with by carrying forward the most recent observation to the end point.

This study will use the IBM SPSS Statistics (version 22.0) software for data management and analysis. Professionally-trained dermatologists will collect all data. Members of the research team will perform the data collection and statistical analyses. Quantitative indicators will be expressed as mean ± standard deviation. If the sample is normally distributed and the variance is uniform, the *t* test will be performed: the paired sample *t* test will be used for intra-group comparison, and the independent sample *t* test will be used for inter-group comparison. If the variance is uneven, the approximate *t* test will be used. If the sample is not normally distributed, the rank-sum test (non-parametric) will be applied. The Chi-square test will be used for counting data. *P* values less than .05 will be considered as statistically significant.

The Chinese Ethics Committee of Registering Clinical Trials (Chengdu, China), which does not have any competing interests, will be responsible for monitoring the data. The Department of Science Research of the hospital at Chengdu University of TCM, which is independent of the investigators, will perform data audits in the trial.

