## Discussion

3

Psoriasis is a common chronic recurrent skin inflammatory disease. Psoriasis vulgaris plays a major role in the psoriasis. In the process of clinic, patients with psoriasis vulgaris are also the most common. The visiting time of patients is often in the progressive stage of psoriasis vulgaris, during this period, the original lesions gradually expand, or even fuse into pieces, new lesions continue to appear, which has the most serious impact on patients. With the gradual understanding of the pathogenesis of psoriasis and the continuous improvement of medical level, psoriasis has made great progress in treatment measures, but it is still in the stage of disease control and cannot be completely cured. Most patients need lifelong treatment. Long-term treatment, heavy economic burden, and easy recurrence have become the main factors affecting the quality of life of patients. Therefore, through the study of optimizing the treatment plan of psoriasis, reducing the economic burden of patients and delaying the time of recurrence, it is very important to formulate a reasonable treatment and follow-up plan, take targeted intervention measures and improve the quality of life of patients. The Chinese herb bath can achieve ideal curative effect by penetrating the drugs with warm effect into the skin or meridian points and directly into the meridians and blood vessels, acting on the focus site. After soaking in the bath of Chinese medicine liquid, the skin can remove pollutants such as exudates, crusts and scales, and has the effects of moisturizing and relieving itching, clearing heat and cooling blood, detoxification and convergence; Chinese medicine liquid can dilate the capillaries of patients and improve local microcirculation, promote metabolism, accelerate the repair of affected tissue, and promote the regression of skin lesions. In clinic, the use of Chinese herb bath, or Chinese herb bath combined with other therapies in the treatment of psoriasis is quite common, with high efficiency, definite curative effect, few adverse reactions and good patient compliance.

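### The only safety item named as an outcome is adverse reactions, while section 2.6 uses adverse events; in this open trial the outcome should be the all-cause count

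*Protocol article*

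**What the plan says.** Section 2.5.1 of the protocol article, citing a Chinese guidance document on research into new traditional medicines, says that "the effective rate of treatment, pruritus score, and incidence of adverse reactions are taken as secondary outcomes". This is the only safety item among the named primary and secondary outcomes. The term is not defined.

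Section 2.6 uses another term: "the safety of this study will be evaluated by adverse events, routine blood tests, and liver and kidney function tests". It does not mention reactions.

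On blinding, section 2.2.6 says: "Because the 3 groups’ intervention measures are not the same, blinding methods are not applicable". No blinded assessor is described. Section 2.7 has trained dermatologists collect the data and adds: "Members of the research team will perform the data collection and statistical analyses". No independent assessor of relatedness is named. For categorical data the same section says: "The Chi-square test will be used for counting data", with a significance level of .05.

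The abstract makes the safety of different water temperatures and herbal concentrations an aim of the trial. Its list of parameters to be compared contains neither adverse reactions nor adverse events.

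**The concern.** An adverse event is something that happened to a patient. An adverse reaction, in ordinary trial usage, is an adverse event that someone has attributed to treatment. Randomisation protects the comparison of the first, but not the judgement that turns the first into the second.

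In this trial the people in a position to make that judgement know whether the patient had a hotter or stronger bath, ozone water or no bath. The same dizziness or rash may be called a reaction in one arm and disease or coincidence in another. The Discussion also records an expectation about this kind of endpoint, describing herbal baths in practice as used "with high efficiency, definite curative effect, few adverse reactions and good patient compliance". That is a general remark and does not show that staff will attribute differently by arm, but it is a reason not to rest the named safety outcome on attribution.

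At stake is the between-arm safety comparison. It could move in either direction with belief about the bath, although section 2.6 already covers a count that needs no attribution.

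**Working it through.** **Wording set side by side.**

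| Section | Term | Role | Relatedness judgement |
|---|---|---|---|
| 2.5.1 | adverse reactions | named secondary outcome | needed in the usual sense; not described |
| 2.6 | adverse events, plus blood, liver and kidney tests | safety evaluation | not needed |

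Nothing in the article links the two rows.

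**Figures in the plan.** No rate is stated for either term, so there is no safety figure to reproduce. The group size used below is the stated 36 per arm (8 × 36 = 288, as in section 2.2.3).

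**Illustration 1 (all rates assumed).** Reported reaction incidence = patients with an event × share attributed ÷ 36. Take 8 of 36 patients with an event in both arms.
- All-cause: 8/36 = 22.2% in each arm.
- 75% attributed: 0.75 × 8 = 6, and 6/36 = 16.7%.
- 25% attributed: 0.25 × 8 = 2, and 2/36 = 5.6%.

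The reported incidence differs threefold with no true difference. A single table of 6/36 v 2/36 would not be significant. The pooled rate is 8/72 = 0.111, the difference is 4/36 = 0.111, and its standard error is √(0.111 × 0.889 × 2/36) = 0.0741. So z = 1.5, chi-square = 2.25 and p is about 0.13.

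**Illustration 2 (all rates assumed).** This is the chance of a false-positive result with 36 v 36. It uses the uncorrected two-sided chi-square test at .05 and exact enumeration of both binomial distributions. The true event rate is equal in the two arms, at 10%, 20%, 30% or 40%. The reaction rate in each arm is the event rate × the share attributed.

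| Outcome compared | Share attributed, arm A v arm B | False-positive rate over event rates 10% to 40% |
|---|---|---|
| All adverse events | not applicable | 4.9% to 5.8% |
| Adverse reactions | 50% v 50% | 3.8% to 5.8% |
| Adverse reactions | 70% v 50% | 6.0% to 12.2% |
| Adverse reactions | 80% v 40% | 10.2% to 35.4% |
| Adverse reactions | 80% v 20% | 18.1% to 75.3% |

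Attribution does no harm to the error rate when it is equal across arms. The harm grows with the gap between arms, and the all-cause comparison is not exposed to it.

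**The case against.** The strongest reply is that this is a difference of wording in a condensed article. No section defines an adverse reaction, describes an assessment of relatedness or says who would make one. The article also uses the term loosely for harms in the Introduction and the Discussion, so the two terms may mean the same count. Definitions and causality rules commonly sit in a full protocol or analysis plan, which is not shown. This stands as a limit on the claim: the need for a relatedness judgement is inferred from the ordinary meaning of the word. It does not remove the point, because the article itself fixes the outcome, and the same sentence would correct it under either reading.

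A second reply is that an all-cause count in an open trial is not automatically fair either. Section 2.3.5 has nurses ask patients about symptoms around the herbal bath, and no matching questioning is described for patients on basic treatment alone. This stands in full: the change removes attribution bias but not unequal ascertainment.

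Two stronger readings are tempting, and the article does not support them.
- A reader might infer that all-cause events are discarded, or that only reactions are compared between arms. Section 2.6 keeps adverse events in the safety evaluation, and no section limits the comparison to reactions.
- A reader might infer that the basic-treatment arm can have no countable reactions. All arms receive two oral medicines and a topical oil (sections 2.3.1 and 2.3.2), so reactions to trial treatment can occur in every arm.

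**Conclusion.** The point holds in a limited form. Sections 2.5.1 and 2.6 use different safety terms without reconciling them, and the one designated as an outcome would, in its usual sense, depend on a judgement by staff who know the arm.

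Its size cannot be taken from the article. The 17% v 6% figure and the false-positive rates rest wholly on assumed event rates and attribution shares. They show how the bias would work, not how large it will be. If staff attribute equally in all arms, or if the two terms are synonyms here, the error rate is not inflated.

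Only a secondary outcome is affected, and PASI as primary outcome is untouched. The change is still worth making, because safety is a declared aim and the correction is cheap.

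**What to change.** In section 2.5.1, replace the incidence of adverse reactions with the proportion of randomised patients who have at least one adverse event after the start of treatment, regardless of cause. Take it from the events already covered by section 2.6, and apply the same definition in all eight arms. Keep investigator-attributed reactions as a descriptive listing only.

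The cost is one sentence and no new category of safety data. The reported incidence will be higher, because unrelated events are counted in every arm. The result should also be read knowing that the article describes symptom questioning only around the bath, so detection of events may still differ between arms.
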